## Abstract

**Background:**

Endometriosis is a chronic disease characterized by growth of endometrial tissue outside the uterine cavity which could affect 200 million women (The term “woman” is used for convenience. Individuals gendered as man or as nonbinary can also suffer from this disease) worldwide. One of the most common symptoms of endometriosis is pelvic chronic pain associated with fatigue. This pain can cause psychological distress and interpersonal difficulties. As for several chronic diseases, adapted physical activity could help to manage the physical and psychological symptoms. The present study will investigate the effects of a videoconference-based adapted physical activity combined with endometriosis-based education program on quality of life, pain, fatigue, and other psychological symptoms and on physical activity.

**Methods:**

This multicentric randomized-controlled trial will propose to 200 patients with endometriosis to be part of a trial which includes a 6-month program with 45 min to more than 120 min a week of adapted physical activity and/or 12 sessions of endometriosis-based education program. Effects of the program will be compared to a control group in which patients will be placed on a waiting list. All participants will be followed up 3 and 6 months after the intervention. None of the participants will be blind to the allocated trial arm. The primary outcome measure will be quality of life. Secondary outcomes will include endometriosis-related perceived pain, fatigue, physical activity, and also self-image, stereotypes, motivational variables, perceived support, kinesiophobia, basic psychological need related to physical activity, and physical activity barriers. General linear models and multilevel models will be performed. Predictor, moderator, and mediator variables will be investigated.

**Discussion:**

This study is one of the first trials to test the effects of a combined adapted physical activity and education program for improving endometriosis symptoms and physical activity. The results will help to improve care for patients with endometriosis.

**Trial registration:**

ClinicalTrials.gov, NCT05831735. Date of registration: April 25, 2023

**Supplementary Information:**

The online version contains supplementary material available at 10.1186/s13063-023-07792-1.

## Administrative information

Note: the numbers in curly brackets in this protocol refer to SPIRIT checklist item numbers. The order of the items has been modified to group similar items (see http://www.equator-network.org/reporting-guidelines/spirit-2013-statement-defining-standard-protocol-itemsfor-clinical-trials/).

## Introduction

### Background and rationale {6a}

Endometriosis is a chronic disease characterized by growth of endometrial tissue outside the uterine cavity which affects approximately 10% of women of reproductive age worldwide [1]. One of the most reported symptoms of endometriosis is pelvic chronic pain, associated with fatigue. Infertility could also be one of the symptoms. These symptoms can cause psychological distress and interpersonal issues that are as difficult to live with as the pain itself. Compared to women who do not suffer from endometriosis, women with this disease develop a lower sense of femininity, altered body image, higher levels of stress, depression, and anxiety [2, 3]. These factors affect their QoL [4] and can have negative impacts on the response to treatment [5]. Interpersonal relationships are also impacted such as romantic [6, 7], professional [8], and social relationships [9], because the symptoms make it difficult to move and carry out daily activities [10].

This disease generates significant health care costs (e.g., 9.5 billion in France, 7.4 billion in Australia) because there is no curative therapy for it, and its management involves long-term pain-related pharmaceutical treatment and/or iterative surgery, which remain palliative care [11]. However, research showed that these treatments are only relatively effective in reducing pain [12, 13] and that this disease or its symptoms have high recurrence rates (e.g., 2.7% to 6.3% of rehospitalization after surgery at least one at 1 year [14]). These results invited to go further and to include complementary therapies as an adjunction in the pain management to increase health care efficacy [15].

Recent articles highlighted the beneficial effects of regular physical activity (PA) and adapted physical activity (APA) on chronic diseases [16, 17]. Research suggested that (A)PA may have a beneficial effect on the physical symptoms and the psychological and social consequences of these diseases [18, 19], thus maybe also in endometriosis context. However, studies questioning the link between PA and endometriosis (and its symptoms) are rare, mostly cross-sectional, and their results are inconsistent [20–22]. The scarcity of studies can be explained by the painful symptoms caused by the disease, leading women not to practice much PA spontaneously and autonomously or even avoid practicing. In addition to this difficulty, widely recognized barriers to PA (i.e., lack of time, lack of adequate and nearby infrastructure, and low self-confidence and motivation for PA) can also contribute to the low level of PA [16]. Otherwise, due to their cross-sectional design, it was not possible for these studies to establish a causal link between PA and endometriosis-related symptoms. Randomized controlled trials (RCT) are needed to test the effects of (A)PA on the endometriosis symptoms and its consequences.

Prior report highlighted the beneficial effects of regular PA and particularly PA adapted to motor abilities with regard to the disease, called APA, on chronic diseases [16]. What differentiates PA from APA is that in addition to being based on health recommendations, APA is offered by qualified personnel and includes motivational and educational components aimed at promoting a healthy lifestyle. (A)PA appears to reduce pain severity and improve physical functioning [19]—particularly through its anti-inflammatory effects [16]—reduce fatigue [23, 24], and enhance psychological and social health [18].

In endometriosis setting, in vivo experiments on animal models such as mice and rats have tested the effects of PA. Results showed that PA may reduce oxidative stress, reduce the development of the disease and the size of endometriotic lesions, and has an anti-inflammatory effect (e.g., [25–27]). To our knowledge, six other studies (RCT) investigated the effects of PA on endometriosis and endometriosis symptoms on humans. In two clinical trials (NCT03994432 and NCT05091268), researchers investigated the role of PA, specifically. They evaluate whether a dietary recommendation based on the Mediterranean diet’s principles associated with a regular aerobic PA, according to the “7 minutes workout” (12 high-intensity physical exercises, lasting 30 s each and spaced out 10 s of short breaks, to be performed 2–3 times a week), may improve pain symptoms in patients with symptomatic endometriosis, treated with estrogen-progestins or progestins (*N* = 140). The choice of this type of PA is based on one well-known barrier of PA, that is, the lack of time. They also aim to study the effect of pain education and group-based PA versus pain education alone on women with endometriosis-associated pain. Participants (*N* = 78) will all attend a four-hour pain education session, while the intervention group also receives a 60-min weekly group training session led by a physiotherapist and a progressive home exercise program performed daily over a period of 4 months. Exercise will focus on general strength and cardiovascular fitness, stretching, and relaxation (NCT05091268). Results from those studies have not been published yet. Two protocol studies [28, 29] planned (I) to explore the potential benefits of a therapeutic exercise program on the health-related QoL (*N* = 26) and (II) to assess the efficacy of yoga and cognitive–behavioral therapy, above education, on quality of life, biopsychosocial outcomes, and cost-effectiveness (*N* = 228), respectively. Another study [30] tested the effect of a 24-week PA program on patients who benefited from a medical treatment (*N* = 36). The results showed a decrease of the treatment side effects in the PA group (muscle cramps, back pain, headache, fatigue) but no significant difference in psychological symptoms or time to recurrence. Finally, a pilot study (*N* = 22) aimed to investigate the impact of a single session of “supervised” telehealth-delivered exercise compared to “self-managed” virtual reality (VR)-delivered exercise on pelvic pain [31]. The “supervised” telehealth-delivered exercise consisted in a 1-h supervised session that included cardiorespiratory exercise (interval training) and stretching. The “self-managed” virtual reality (VR)-delivered exercise consisted in a 1-h unsupervised session with (i) a 10-min VR pain-distraction experience and (ii) 50 min of exercise using a PA application. These interventions were compared to a control group (non-intervention). Results showed no difference between groups but highlighted a more favorable score for the groups with intervention compared to the control group. The PA proposed in these studies was not APA.

It is worth noticing that only three of these studies used educational and/or psychological sessions to be part or complement of PA sessions in their program. However, it has been proven that PA program accompanied by an educational program is more effective [16, 32, 33]. Furthermore, none of these studies make it possible to assess the specific role and mechanisms of action of each component of the program (e.g., APA, educational sessions), which makes it impossible to identify the effective leverages of intervention. Otherwise, for each of these studies, all or part of participants need to go on site to benefit from the PA program. However, barriers of PA are related to time, proximity, accessibility, and, in chronic diseases, to some symptoms (i.e., pain, fatigue that can reduce the ability to drive or commute to the places in which PA sessions are delivered). In this context, new technologies could be a promising lever. APA delivered via videoconferencing showed lower attrition, a good completion rate, and high satisfaction with the program [34]. What participants enjoyed were the organizational simplicity and the possibility to hide the disease and build a social link [35]. The low number of results from RCT studies which did not propose post-intervention follow-up, the cross-sectional design of most studies about PA and endometriosis, led us to propose the CRESCENDO (inCRease physical Exercise and Sport to Combat ENDOmetriosis) program, an RCT, with 6 months follow-up, to test the effects of combined (A)PA and endometriosis-based education delivered via videoconference on endometriosis symptoms and its consequences.

### Objectives {7}

The trial objectives will be (I) to test the effects of a “APA + endometriosis-based education” in improving QoL, but also in decreasing perceived pain and fatigue and in increasing PA, (II) to investigate potential predictor and mediator/moderator variables of treatment outcomes, and (III) to help in improving medical, physical, and psychological care for patients by proposing a structured program and by using videoconference to reduce barriers to PA.

### Trial design {8}

The study will be a multicentric randomized-controlled superiority trial which will include four arms (i.e., “APA,” “education,” “APA + education,” and “waitlist control group”) and will test the effect of a 6-month program on QoL in patients with endometriosis. The efficacy of the program in intervention groups will be compared to a control group (i.e., waitlist group control) which will benefit from APA and education sessions at the end of the 6 months program. Randomization will be balanced with a 1:1:1:1 ratio for patients’ allocation to the three intervention groups and the waitlist control group. Identifying potential moderators and mediators of treatment outcome will also be a component of this trial.

## Methods: participants, interventions, and outcomes

### Study setting {9}

Patients with endometriosis will be recruited in French speaking countries (e.g., France, Canada, Switzerland, Belgium). Participants will use their own new technology devices (e.g., notebook, PC, tablet, laptop) to access and attend the videoconferencing APA and/or education sessions. The schedule of the study is presented in Fig. 1.

**Fig. 1 Fig1:**
[figure not shown]
SPIRIT study schedule. *t*_5_ is the last time of measurement and the endline assessment

### Eligibility criteria {10}

The inclusion criteria are as follows:Endometriosis diagnosed (by physical exam, MRI)Age > 18 and sexually activeModerate to significant functional difficulties, pain, and fatigue (between 4 and 10/10 points on visual analogue scale)Sufficient French language skillsFree access to the Internet with a stable Internet connection on a device which allow to see movement and be seen (webcam)

The exclusion criteria are as follows:Disabling disease other than endometriosis with the same major symptoms (cancer, arthritis, ...)BMI ≥ 40No major difficulties related to the diseaseParticipation to another program which propose education and/or PA program at the same time that the CRESCENDO programSurgery or medically assisted procreation scheduled within 9 months

### Who will take informed consent? {26a}

Informed consent will be managed by the principal investigator (PI). Patients will be informed by their endometriosis specialists in one of the French health centers partners to this program (i.e., La Croix Rousse Hospital Lyon, Strasbourg Hospital, Grenoble Hospital, Nimes Hospital, Mulhouse Hospital) of the existence of the program, and the latter will give them a flyer of the program with the PI’s email. Once the email is received, the PI will send the consent form containing written information about study (e.g., aim, duration, data collections during and after the program, randomization process) and will invite the potential participants to discuss the program via a one-to-one scheduled videoconference (will also allow to ensure the technology and Internet access). This first videoconference contact will last 30 min. This meeting will allow to extensively present the study and answer potential participant’s questions. Then, participants will be asked to send written informed consent when they want (within a few hours, days, or weeks) to ensure that consent is given without any pressure and to leave time to read again the written information.

### Additional consent provisions for collection and use of participant data and biological specimens {26b}

This trial does not involve collecting biological specimens for storage.

## Interventions

### Explanation for the choice of comparators {6b}

The comparator will be the waitlist control group. As much as all participants, those in the waitlist control group will continue with their usual treatment and activities during their participation to the study (e.g., hormonal treatment, antalgic treatment, PA, physiotherapy). The allocation in a group being done randomly, and because each endometriosis case is unique in terms of symptoms and treatment, using a waitlist control seemed relevant to compare the effects of the interventions on participants with similar characteristics. For ethical reasons, the waitlist control group will benefit from the intervention after the and on the main intervention (i.e., 6 months after they start the program).

### Intervention description {11a}

All participants in the study will receive a personalized PA assessment (physical tests) after inclusion, before the start of the program. This assessment will be conducted by an APA teacher. A booklet on PA recommendations, in particular the health benefits of PA and the latest studies on PA and endometriosis, will be given to all participants. This booklet will also include a link to a video of movements to perform. Participants will receive a second PA assessment at 6 months (end of the intervention).

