#### Functional capacities

Physical assessment consisted of 2 minutes knee raise test (cardiorespiratory endurance), the Unipedal Stance Test (UPST) (balance and proprioception), Back Scratch Test (high flexibility), 30 s Chair Stand Test (explosive strength of lower limbs), and Sit and Reach (low flexibility).

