### Concealment mechanism {16b}

Each participant will be entered in the database to be allocated only once the consent form and the baseline online questionnaire are completed and sent to the principal investigator. Thus, each participant will be included chronologically, the date and hour of the last document sent in the principal investigator’s mailbox being the references. The principal investigator is the only one to know when the document was received. Allocation concealment will be ensured as R script will not release the randomization code until the patient has been included into the trial.

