### Implementation {16c}

Randomization will be implemented by the principal investigator. Participants will receive an email to inform them about their allocation.

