## Assignment of interventions: blinding

### Who will be blinded {17a}

Regarding the design of the intervention, researchers and participants will not be blinded to the allocated trial arm.

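### Baseline physical tests fall after the allocation trigger, so the arm can be known when the baseline of an effort-dependent secondary outcome is measured

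*Protocol article*

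**What the plan says.** All references are to the protocol article.

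- **Timing of the tests.** Intervention description {11a}: "All participants in the study will receive a personalized PA assessment (physical tests) after inclusion, before the start of the program". The same section adds: "This assessment will be conducted by an APA teacher". A second assessment follows at 6 months.
- **Allocation trigger.** Concealment mechanism {16b}: each participant is entered "to be allocated only once the consent form and the baseline online questionnaire are completed and sent to the principal investigator". The order of inclusion is set by when the last of these documents arrives, and the "R script will not release the randomization code until the patient has been included into the trial".
- **Disclosure.** Implementation {16c}: "Participants will receive an email to inform them about their allocation". No time is given for that email relative to the physical tests.
- **Blinding.** Who will be blinded {17a}: "researchers and participants will not be blinded to the allocated trial arm".
- **Status of the tests.** The Functional capacities section, placed under Secondary outcome measures, begins: "Physical assessment consisted of 2 minutes knee raise test". It goes on to a one-leg stance, a back scratch test, a chair stand test and a sit-and-reach test. Secondary outcome measures sets a baseline value for the secondary outcomes.
- **Analysis.** Statistical methods {20a} plans general linear and multilevel models that compare groups with repeated measures, at two-sided 0.05.

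**The concern.** A baseline is safe from influence by the allocation only if it is recorded before anyone who can affect it knows the allocation. The protocol applies that rule to the online questionnaire but not to the physical tests, and gives no reason for the difference.

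Knee raises in two minutes and chair stands in 30 seconds depend on how hard the participant tries and how much the tester encourages her. A participant who knows that she has been given the APA program may try harder at the first test. One who knows that she must wait may try less. Either reaction opens a gap between the arms at baseline that randomization did not create and that is not a treatment effect. A change score carries that gap in full into the estimate. A baseline-adjusted model carries part of it, because it treats the gap as a chance imbalance to be corrected.

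**Working it through.** **Order of events as written**

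1. The consent form and the online questionnaire reach the principal investigator. This completes the trigger for allocation ({16b}).
2. The patient is included, and from then on the script may release the code ({16b}).
3. The participant is told her arm by email, at an unstated time ({16c}).
4. The physical tests take place after inclusion and before the program starts ({11a}).

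The tests are not part of the trigger in step 1 and come after step 2. No section places step 4 before the release of the code or before step 3. Knowledge of the arm at the baseline test is therefore possible and not prevented.

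**Size, as an illustration**

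The plan gives no figure to reproduce on this point.

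*Inputs from the protocol article:* 200 participants (Sample size {14}) at 1:1:1:1 (Trial design {8}), so about n = 200/4 = 50 per arm; two-sided alpha 0.05 ({20a}), critical value 1.96.

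*Assumptions, not in the documents:*
- Knowing the arm moves the baseline mean of an APA arm above that of the waitlist arm by b = 0.2 SD.
- The correlation between baseline and 6 months is r = 0.6.
- There is no true effect, and the 6-month score carries no shift of its own.

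*Change score:*
- bias = b = 0.20 SD, against APA
- variance per patient = 2(1 − r) = 2 × 0.4 = 0.80
- SE = √(2 × 0.80/50) = √0.032 = 0.179
- bias/SE = 0.20/0.179 = 1.118
- rejection favouring waitlist = Φ(1.118 − 1.96) = 0.200
- rejection favouring APA = Φ(−1.118 − 1.96) = 0.001
- total about 20%

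*Baseline-adjusted (ANCOVA):*
- bias = r × b = 0.6 × 0.2 = 0.12 SD, against APA
- variance per patient = 1 − r² = 1 − 0.36 = 0.64
- SE = √(2 × 0.64/50) = √0.0256 = 0.16
- bias/SE = 0.12/0.16 = 0.75
- rejection favouring waitlist = Φ(0.75 − 1.96) = 0.113
- rejection favouring APA = Φ(−0.75 − 1.96) = 0.003
- total about 12%

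Without a shift, each direction has 2.5%. The chance of falsely declaring an APA benefit therefore falls, to about 0.1% and 0.3%, and the excess lies almost wholly on the waitlist side.

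*Range, same formulas, n = 50:*

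| Shift b | r | Change score: bias, rejection rate | ANCOVA: bias, rejection rate |
|---|---|---|---|
| 0.1 | 0.5 | 0.10 SD, 8% | 0.05 SD, 6% |
| 0.2 | 0.6 | 0.20 SD, 20% | 0.12 SD, 12% |
| 0.2 | 0.7 | 0.20 SD, 25% | 0.14 SD, 17% |
| 0.3 | 0.8 | 0.30 SD, 66% | 0.24 SD, 52% |

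Adjusting for baseline reduces the bias but does not remove it. A comparison of 6-month scores that ignored the baseline would not be affected by a baseline shift.

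**The case against.** **The order is not fully stated.** The sentence about the script gives the earliest time at which the code can be released. It does not say that release or disclosure comes before the tests. The allocation email has no stated time, and the two schedule figures, which may show the order, are not available here. This stands: a reader might infer that every baseline test is done with the arm known, and the text does not support that.

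**The teacher's knowledge is inferred.** The blinding section speaks of researchers and participants and does not name APA teachers. In the APA arm, the teacher presents the personalized program after the assessment. This also stands, so the teacher's knowledge is a possibility and not a stated fact. It does not close the gap, because a participant who has had the email can change her own effort whatever the tester knows.

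**The outcome is minor.** The tests are missing from the abstract's list of secondary outcomes, and they also serve to grade participants' level at inclusion. That limits the importance of the point. The section on them still sits under the secondary outcome measures.

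**The bias would not favour the intervention.** This stands for the two reactions described. A reader might take the rejection rates above as a risk of falsely claiming that APA works. Almost all of the excess points the other way. In a superiority trial, the practical harm is a real benefit understated or missed.

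**Arm-dependent loss between allocation and testing.** A reader might add this as a further bias. It could happen, but nothing in the document bears on it, and the point does not rest on it.

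**Conclusion.** The point holds in a limited form. Followed as written, the plan leaves the baseline of one listed, effort-dependent secondary outcome unprotected from knowledge of the arm. Some unblinded assessment at 6 months is hard to avoid in an exercise trial, but an unprotected baseline can be avoided.

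The primary outcome is untouched: baseline quality of life is self-reported online, and the baseline online questionnaire must be complete before allocation.

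The documents do not show that a shift will occur or how large it would be. The central illustration rests wholly on the assumed shift, correlation and clean 6-month score. If the same shift were present at both visits, it would cancel in a change score. The direction, mainly towards hiding an APA benefit, follows from assuming more effort in APA arms or less on the waitlist.

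**What to change.** - In Concealment mechanism {16b}, add the completed physical assessment as a third item that must be in hand before the randomization script is run.
- In Intervention description {11a}, change the timing of the first assessment from after inclusion to *after consent and before allocation*.

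If the tests are in practice already done before the code is released, one sentence saying so closes the point.

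**Cost.** Everyone allocated is tested anyway, so only the order changes. Allocation has to wait for the test, and a few people who are tested may not go on to allocation.
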